**Table 3 T3:**
[figure not shown]
Schedule of evaluations during the study.

## Discussion

3

As a U-shaped relationship of systolic BP and outcomes after IV-tPA is suggested in various studies,^[8,10,12]^ both high and low systolic BP are considered harmful. Interestingly, the nadir for optimal outcome appears to be a systolic BP of 140 to 160 mm Hg. Thus, we hypothesize this systolic BP as being the best target for functional outcome and reduced risk of sICH.

Labetalol was chosen for BP lowering because of ready availability, minimal adverse effects on heart rate, and cardiac output due to being a mixed α and β antagonist effects, rapid onset of action (5 minutes) and reasonable duration of action (3–6 hours). Studies indicate stable effects of labetalol on CBF, cerebral oxygen consumption, and cerebral circulation.^[21,22]^ There is good experience of the use of labetalol in patients with AIS^[23]^ and it has a predictable and uniform dose-response relationship.^[23]^

With serial BP measurements (including comparison of different intensities of BP lowering), NIHSS and repeated CT perfusions, this study will provide mechanistic data to elucidate the relationship between BP, cerebral perfusion, and functional outcomes in thrombolysed AIS cases. Our findings may assist the ongoing studies (such as ENCHANTED BP intensity arm results due in early 2019) and improve the design of future clinical trials of BP management in AIS (in thrombolysed and endovascularly treated) patients.

Finally, we wish to clarify that study is not aimed at evaluating the relationship between early intensive BP reduction and arterial recanalization or persisting occlusion. Study participants are recruited after the arterial recanalization treatment strategies (IV thrombolysis and/or EVT) have already been implemented. While the first CT perfusion serves as the baseline for a particular patient, subsequent perfusion scans provide information about the longitudinal changes in cerebral hemodynamic parameters in response to the changes in BP levels.

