## Introduction and rationale

1

Elevated systolic blood pressure (BP), defined as >140 mm Hg, is commonly observed in patients with acute ischemic stroke (AIS).^[1]^ Potential mechanisms and associations include pre-existing hypertension,^[1]^ activation of neuroendocrine systems,^[2]^ stress of hospitalization,^[3]^ location of the infarct,^[4]^ stroke subtype,^[5]^ severity,^[6]^ and a homeostatic response to raised intracranial pressure.^[7]^ Whether treatment of this acute hypertensive response improves clinical outcome is unknown.^[7,8]^ Arguments in favor of treatment include the strong positive relationship between degree of elevation in BP and death or dependency,^[9]^ cerebral edema,^[10]^ early and late stroke recurrence,^[11,12]^ and extrapolation of potential benefits in acute intracerebral hemorrhage (ICH).^[13–15]^ Arguments against treatment center on the natural tendency for BP to normalize within a few days of presentation,^[1,5,6]^ and potential harms associated with altered cerebral perfusion related to dysfunction of autoregulation.^[7,16,17]^ Some studies suggest that adverse outcomes are associate with early antihypertensive therapy.^[18,19]^

The primary aim of the study is to determine the effect of early intensive BP lowering (systolic BP target 140–160 mm Hg) initiated within 6 hours of symptom onset and maintained for 72 hours in AIS patients treated with intravenous tissue plasminogen activator (IV-tPA) on cerebral blood flow (CBF), measured with computed tomographic (CT) perfusion imaging. We hypothesize that this treatment approach is safe and that such magnitude of BP lowering does not reduce CBF by 20% and/or increase the volume of hypoperfused tissue by >20% on CT perfusion or adversely affect functional outcomes at 90 days. Secondary aims are to obtain preliminary estimates of the clinical impact of early intensive BP lowering on functional outcomes and symptomatic intracerebral hemorrhage (sICH).

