### Randomization and blinding

2.3

All study subjects undergo CT perfusion to obtain the baseline cerebral hemodynamic parameters. Participating patients are randomly assigned to early intensive BP lowering (140–160 mm Hg) or the guideline-based management (160–180 mm Hg) in a 1:1 ratio using a central computer generated sequence with minimization according to age (<60 vs ≥60 years), severity (NIHSS score <10 vs >10), and baseline systolic B (<150 vs >150 mm Hg). The treating physician is unblinded to the treatment assignment as he/she is required to titrate BP control with IV labetalol. However, all 90-day outcome assessments are conducted by physicians who are kept blind to the treatment allocation.

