### Background care

2.5

All patients will be managed in a high-dependency stroke unit with repeated neurological examination using the NIHSS, noninvasive BP, and heart rate monitoring (consistent recordings using automatic devices, every 15 minutes for 1 hour, then hourly for 23 hours, then 6 hourly until discharge). All BP measurements are obtained from the nonparetic arm. Rescue endovascular intervention (before inclusion into the study and randomization) is allowed according to local institutional practice. Figure 1 describes the workflow in the study.

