### Data collection and follow-up

2.6

All patients undergo repeat CT-perfusion scans at 24 and 72 hours postrandomization, to obtain the estimates of the effects of BP on various cerebral perfusion parameters. NIHSS scores are assessed daily until day 7 (or hospital discharge, if earlier) (Table 2). Patients are followed-up at day 90, where the NIHSS and mRS scores are reassessed. These assessments are conducted in-person by trained staff who are blind to the treatment allocation.

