### Outcomes

2.7

The primary outcome is the assessment of CT perfusion studies and evaluate whether CBF in the affected region reduces by >20% and/or the volume of hypoperfused tissue increases by >20% if BP is treated intensively during the first 72 hours in thrombolysed AIS patents. Secondary endpoint is dependency at day-90, defined by scores 2 to 6 on the mRS. Secondary outcome would be sICH, defined by the Safe Implementation of Thrombolysis in Stroke-Monitoring Study (SITS-MOST) criteria as large local or remote parenchymal ICH (type 2) combined with a neurological deterioration (≥4 points on the NIHSS) from baseline or death within 36 hours.^[20]^ Data are entered prospectively on to case report forms without any personal identifiers.

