### Sample size calculations

2.11

Allowing for within-subject and between-subjects variation, a sample size of 27 patients per group was estimated to allow detection of a difference of 20% [15% standard deviation (SD)] in relative change in CBF and/or the volume of hypoperfused tissue between the early intensive BP lowering and control groups, with 90% power and significance set at 5% (α = 0.050, 2-tailed). The sample size was increased to 30 patients per group to allow for treatment dropouts, crossovers, and potential loss to follow-up.

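### The primary criterion is worded as change within the intensive arm, while the trial is sized and analysed on the difference between arms; shared reperfusion can make the two disagree

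*Protocol article*

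**What the plan says.** **Criterion.** Protocol article, 2.7 Outcomes, gives the primary outcome as an assessment of the CT perfusion studies to "evaluate whether CBF in the affected region reduces by >20% and/or the volume of hypoperfused tissue increases by >20% if BP is treated intensively". No control arm appears in the sentence. The hypothesis in the Introduction has the same form: the blood pressure lowering "does not reduce CBF by 20% and/or increase the volume of hypoperfused tissue by >20% on CT perfusion". The Abstract repeats it.

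**Interpretation.** Section 2.6 (Data collection and follow-up) says that the 24- and 72-hour scans are done "to obtain the estimates of the effects of BP on various cerebral perfusion parameters". The Discussion calls the first scan the patient's own baseline and adds that "subsequent perfusion scans provide information about the longitudinal changes in cerebral hemodynamic parameters in response to the changes in BP levels".

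**Sizing and analysis.** Section 2.11 sizes the trial on a "difference of 20% [15% standard deviation (SD)] in relative change in CBF and/or the volume of hypoperfused tissue", and the contrast that it names is the one "between the early intensive BP lowering and control groups". Section 2.12 analyses by intention to treat and compares relative changes, CBF among them, by ANCOVA.

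**Reperfusion treatment.** All patients have had intravenous thrombolysis. Section 2.5 adds: "Rescue endovascular intervention (before inclusion into the study and randomization) is allowed according to local institutional practice". Section 2.12 names covariates for the blood pressure and stroke severity analyses and none for CBF.

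**The concern.** The criterion in 2.7 can be read as a rule on the intensive arm alone: take the change from baseline and see whether it passes 20%. The Discussion supports that reading, because it treats change since the patient's first scan as the response to blood pressure. In patients who have just had reperfusion treatment, CBF and deficit volume can change over 72 hours for other reasons, such as late recanalization, continuing reperfusion or completion of the infarct. Change from baseline then mixes the blood pressure effect with that course.

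The stake is the safety conclusion. The trial sets out to show that intensive lowering does not cost 20% of perfusion. Reperfusion in both arms would offset a real loss, and the intensive arm could pass the literal criterion while being worse than control by the trial's own threshold. A shared fall of more than 20 points would do the opposite and signal harm with no blood pressure effect at all.

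**Working it through.** **Inputs from the article:** threshold 20%; SD of relative change 15%; 27 per group; 90% power; two-sided 5% (2.7 and 2.11). **Assumed:** the shared change R, the thrombectomy share and the thrombectomy effect, none of which the article gives.

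**The plan's own figure.** With the stated inputs, n per group = 2 × (1.960 + 1.282)² × (15/20)² = 2 × 10.51 × 0.5625 = 11.8. That is 12 per group, or 13 with the t distribution; the article states 27. This mismatch is a separate matter and neither supports nor weakens the present point. What matters here is that 2.11 defines the sized quantity as a difference between groups.

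**Two readings of one result.** Let R be the change in CBF that both arms share, and let the true effect of intensive treatment be -20 points.

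- Own-baseline reading (2.7, Discussion): R - 20
- Between-arm reading (2.11, 2.12): (R - 20) - R = -20

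| Shared change R (assumed) | Control arm | Intensive arm, own change | Intensive minus control |
|---|---|---|---|
| 0 | 0 | -20 | -20 |
| +10 | +10 | -10 | -20 |
| +20 | +20 | 0 | -20 |
| +30 | +30 | +10 | -20 |

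**Chance that the own-baseline reading signals harm.** The standard error of one arm's mean is 15/√27 = 2.89. The probability that the intensive arm's observed mean falls below -20 is Φ((-20 - (R - 20))/2.89) = Φ(-R/2.89). At R = 0 this is 50%. At R = 10 it is Φ(-3.46), about 0.03%, and at R = 20 or 30 it is practically zero.

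**Hypoperfused volume.** The same holds with signs reversed. If both arms shrink by 10, 20 or 30 points and intensive treatment adds 20, its own change is +10, 0 or -10, and the difference is +20.

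**Scale.** Points of relative change are used because 2.11 is written on that scale. If the loss is instead a ratio to control, the intensive arm's own change is (1 + R) × 0.8 - 1 = -12%, -4% or +4% for R = 10%, 20% or 30%. It still misses the line. On the 2.11 scale, however, those cases are differences of -22, -24 and -26 points, which lie beyond the threshold rather than at it.

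**Precision from a thrombectomy covariate.** Suppose 15 is the SD among patients with the same thrombectomy status, a share q had thrombectomy, and it shifts the CBF change by g points. The unadjusted SD is √(15² + q(1 - q)g²).

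| q | g | Unadjusted SD | Power, 27 per arm, unadjusted |
|---|---|---|---|
| 20% | 20 | √289 = 17.0 | 98.9% |
| 30% | 40 | √561 = 23.7 | 86.1% |
| 50% | 40 | √625 = 25.0 | 82.2% |

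With adjustment the SD returns to 15 and power to 99.8%. If 15 already includes this variation, unadjusted power is 99.8% on the stated inputs and there is little left to gain.

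**The case against.** **The randomized comparison is already in the plan.** Section 2.11 sizes it, 2.12 analyses CBF change between groups by ANCOVA under intention to treat, and no section specifies a one-arm test against baseline. A shared change cancels in that comparison. This stands. A reader might infer that reperfusion biases the planned analysis; the article does not support that.

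**The hypothesis can be read causally.** To say that lowering does not reduce CBF implies a contrast with not lowering. That is fair to the Introduction. The Outcomes wording is less easily rescued: the threshold applies to change in the affected region under intensive treatment, and the Discussion then ties change since baseline to blood pressure.

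**The Discussion sets no decision rule.** It also says that recanalization is not a study question and that reperfusion treatment comes before recruitment. This is true, and much of the immediate effect of that treatment should already be in the baseline scan. It does not stop perfusion from changing afterwards.

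**Thrombectomy.** A reader might infer that it is unbalanced between arms and biases the result, because minimization is done "using a central computer generated sequence with minimization according to age (<60 vs ≥60 years), severity" and baseline systolic pressure only. The article does not support this. Thrombectomy takes place before randomization, so it is balanced in expectation. What remains is chance imbalance, which ordinary standard errors allow for, and some loss of precision. Any figure for a shift would rest on a thrombectomy effect with no source. Nor does the absence of a covariate for CBF count as an omission, since an article commonly leaves this to the full protocol or SAP. A fourth minimization factor in a trial of 54 to 60 patients is a debatable trade-off and is not proposed.

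**Conclusion.** The concern holds as an inconsistency in the primary outcome. Section 2.7, with the Abstract and Introduction, states the 20% threshold without a comparator, and the Discussion attributes change since the patient's own baseline to blood pressure. Sections 2.11 and 2.12 concern the difference between arms. Read literally, the 2.7 criterion misses a true 20-point loss of CBF in nearly every trial once both arms gain 10 points or more, while the between-arm difference remains -20. That size rests on an assumed shared gain of 10 to 30 points, an additive effect, and the article's SD of 15 with 27 per arm.

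It does not follow that the planned ANCOVA is biased or that thrombectomy is systematically unbalanced. The thrombectomy covariate is a secondary gain in precision whose value depends on figures that the article does not give. The correction is worth making because the criterion decides the safety claim and costs almost nothing to align.

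**What to change.** 1. In 2.7, and to match in the Abstract and Introduction, restate the primary criterion as the intensive-minus-control difference in relative change in CBF, and likewise in hypoperfused volume. Judge each against 20% and analyse it by the ANCOVA of 2.12. That section's list names CBF but not hypoperfused volume, so add the volume.
2. In the Discussion, and in the matching sentence of 2.6, limit attribution to blood pressure to this randomized comparison. Label within-patient associations between blood pressure and CBF as exploratory.
3. As a secondary step, for precision and not as a bias correction, prespecify thrombectomy before randomization (yes/no) as a covariate in the perfusion ANCOVA. If the SAP already does so, nothing more is needed.

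The cost is wording and one degree of freedom. No new scans or data collection are needed beyond recording thrombectomy, which is known at randomization, and the minimization stays as it is.
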